## 11.4 Assessment Endpoints

In Section 8 of this protocol, all clinical and biological endpoints are defined for evaluation of reactogenicity, safety, immunogenicity, at defined visits after the vaccination (assessments during the vaccination period and during the follow-up period). A detailed description of these variables will be provided in the SAP.

*Information contained in this publication is the property of EVI and ICGEB and is confidential and will not be disclosed to third parties without written authorization from EVI and ICGEB. No part of this document may be reproduced, stored in a retrieval system or transmitted in any form or by any means -electronic, mechanical, recording or otherwise - without the prior authorization of EVI and ICGEB*

[figure not shown][figure not shown]

## 11.5 Analysis Methods

### 11.5.1 Statistical Model, Hypothesis Testing and Tests

No statistical hypothesis can be set up for the safety and immunogenicity data as sample size is limited. The analysis shall be descriptive as the sample size does not allow any comparison between groups. Categorical Variables will be summarised by vaccine groups as frequency, percentages and 95% confidence interval. Continuous Variables other than titers and Concentrations will be summarised by vaccine groups as Mean, SEM, Median, Minimum, Maximum, inter-quartile range/range. The proportion of subjects that received three doses without experiencing grade 3 adverse events will be estimated by Exact Binomial proportion (Proportion and 95% confidence interval).

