9. **Haematology:** Blood samples will be collected for haematology assessments (including RBC Count, haemoglobin, haematocrit, MCV, MCH, MCHC, platelet count, TLC and DLC) at screening visit (any time from D-14 through D-1), D28, D56, D180, D208 and D365. Haematology assessments done at Screening Visit (Visit 2) will be considered as screening laboratory assessments for eligibility as well as baseline assessments for safety end-points since haematology assessments will not be done on Day 0 (pre-vaccination). Blood samples for haematology will be collected prior to vaccination on Days 28 and 180.
10. **Serum Chemistry:** Blood samples will be collected for serum chemistry assessments (including potassium, sodium, AST, ALT, direct, indirect and total bilirubin, alkaline phosphatase,  $\gamma$ GT, creatinine, random blood glucose) during screening period (D-14 through D-1), D28, D56, D180, D208 and D365. Serum chemistry assessments done at Screening Visit (Visit 2) will be considered as screening laboratory assessments for eligibility as well as baseline assessments for safety end-points since serum chemistry assessments will not be done on Day 0 (pre-vaccination). Blood samples for serum chemistry will be collected prior to vaccination on Days 28 and 180.

*Information contained in this publication is the property of EVI and ICGEB and is confidential and will not be disclosed to third parties without written authorization from EVI and ICGEB. No part of this document may be reproduced, stored in a retrieval system or transmitted in any form or by any means -electronic, mechanical, recording or otherwise - without the prior authorization of EVI and ICGEB*

[figure not shown][figure not shown]

11. **Direct Coomb's Test:** Direct Coomb's test will be undertaken at Screening Visit (Visit 2) and additionally will be done during the entire study period if the haemoglobin falls below 13 gm/dL.
12. **Peripheral Blood Smear (PBS):** PBS examination will be undertaken for evidence of haemolysis or any haematological disorder at Screening Visit (Visit 2) and additionally during the entire study period along with Coomb's test if the haemoglobin falls below 13 gm/dL.

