### 3 STUDY OBJECTIVES

#### 3.1 Primary Objective(s)

- To evaluate the safety of three (3) different dosages of JAIVAC-1 malaria vaccine (PfMSP-119 and PfF2) formulated with Montanide ISA720 as adjuvant in healthy Indian male subjects between 18 to 45 years of age
- To compare the safety of three (3) different dosages of JAIVAC-1 vaccine (PfMSP-119 and PfF2) formulated with Montanide ISA720 as adjuvant to the safety of the control vaccine (Hepatitis B vaccine) in healthy Indian male subjects between 18 to 45 years of age

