## 4.6 Definition of Study Endpoints

### 4.6.1 Primary Endpoint(s)

The safety profile will be assessed on the basis of the following criteria

- Immediate reactogenicity (any event occurring within the first three (3) hours recorded every 30 minutes after each vaccination, with emphasis on allergic reactions)
- Local and systemic reactogenicity (solicited adverse events occurring from three (3) hours post-vaccination on Day 0 till Day 14 after each dose)
- Any unsolicited adverse events 28 days after each vaccination
- Any Serious Adverse Event (SAE) occurring from the first dose of vaccine till the last follow-up visit.
- Biological safety, 28 days after each vaccination, in reference with the baseline before the first dose, by measuring the following parameters:

- Haematology: RBC count, Haemoglobin\*, Haematocrit/Packed Cell Volume (PCV), MCV (Mean Corpuscular Volume), MCH (Mean Corpuscular Haemoglobin), MCHC (Mean Corpuscular Haemoglobin Concentration), Platelet Count and Total Leukocyte Count (TLC) along with Differential Leukocyte Count (DLC) on Days -14, 28, 56, 180, 208, 365.

\*If the haemoglobin drops below 13 gm/dL, then a direct Coomb's test and a peripheral blood smear/film will be prepared and examined for evidence of possible haemolysis.

- Serum Chemistry: Potassium, Sodium, AST, ALT, Direct, Indirect and Total Bilirubin, Alkaline Phosphatase, Gamma Glutamyl Transpeptidase ( $\gamma$ GT), Creatinine, and Random blood glucose on Days -14, 28, 56, 180, 208, 365.

The Investigator will be responsible for causality assessment i.e. assessment of the relationship of the AE to the assigned study vaccines, using the following definitions: related or not related.

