## 8 SAFETY MONITORING

### 8.1 Introduction

The collection, recording, assessment and reporting of adverse events (AE) and serious adverse events (SAE) represent the core activities for the safety evaluation. These activities are under the direct responsibility of the Investigator.

The recording of adverse events is an important aspect of study documentation as the evaluation of the safety of three (3) intramuscular injections of the investigational vaccine (JAIVAC-1 – Montanide ISA 720 malaria vaccine) in comparison with that of the control vaccine (Hepatitis B vaccine) is the primary objective of this study. The procedure for evaluation of immediate reactogenicity, solicited adverse events and unsolicited adverse events is described Section 7. The investigator is responsible for the detection and documentation of events meeting the definition of an adverse event (AE) or a serious adverse event (SAE) as provided in Sections 8.4 and 8.5 of this protocol. This includes the evaluation of its seriousness, its severity, and the causal relationship to the investigational vaccine and/or concomitant therapy.

At each visit, the investigator will assess whether any AE including laboratory abnormalities has occurred. The investigator shall inquire for unsolicited AEs with non-suggestive questions to the subject at each study visit. The investigator shall attempt to establish a diagnosis of the event based on signs, symptoms and/or other clinical information. The diagnosis shall be recorded as the AE and/or SAE and not the individual symptoms.

If a laboratory abnormality or other abnormal assessment meets the definition of an AE or SAE, the Adverse Event or Serious Adverse Event Form shall be completed as appropriate. A diagnosis, if known or clinical signs and symptoms if diagnosis is unknown, rather than the laboratory abnormality shall be reported. If no diagnosis is known and clinical signs and symptoms are not present, then the abnormal finding shall be recorded. The subject shall be observed and monitored carefully until the AE resolves, the condition stabilises or its cause is identified completely. The investigator is responsible for ensuring that follow-up includes any supplemental investigations that may be indicated to elucidate the nature and/or the cause of the event.

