#### 11.5.1.1 Analysis of Demographics and Other Baseline Characteristics

Demographic characteristics (age, race etc.) will be tabulated by vaccine group on the ITT data set. Quantitative demographic variable age will be described as number of subjects, mean, SEM, minimum, median, maximum, and range. Qualitative demographic variables will be described by number of subjects and percentage by each vaccine group. Group comparisons will be performed to confirm whether the vaccine groups are similar with regard to demographic characteristics. Clinical laboratory results will be tabulated by vaccine group using both quantitative (raw values) and qualitative parameters (relative positions regarding normal ranges in use in the laboratory). The investigator will check the biological parameters (haematology and serum chemistry) and the vital signs. The clinically significant abnormalities will be described. Concomitant diseases at the first visit will be tabulated by vaccine group using the latest version of MedDRA Adverse Event Dictionary.

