#### 11.5.1.3 Analysis of Overall Safety

The safety analysis will include all randomised subjects who have received at least one dose of either of the assigned study vaccines. The overall percentage of subjects with at least one reported adverse event / serious adverse event, with date of onset up to 28 days after vaccination will be tabulated with 95% confidence intervals, by type of adverse event; by severity; and by causality. These events will be summarised and classified by System Organ Class and preferred term MedDRA. They will be displayed by vaccine group as both frequencies and percentages on the ITT data set. All reported adverse events that start post-vaccination would be tabulated. If a given disease is already reported as ongoing at the first visit on the medical history pages, it will be counted and tabulated as a vaccine emergent adverse event only if it worsens after the vaccination with the study vaccines. For each vaccine group vital sign parameters will be summarised visit wise as number of subjects, mean, SEM, median minimum, maximum and range. The changes in vital

*Information contained in this publication is the property of EVI and ICGEB and is confidential and will not be disclosed to third parties without written authorization from EVI and ICGEB. No part of this document may be reproduced, stored in a retrieval system or transmitted in any form or by any means -electronic, mechanical, recording or otherwise - without the prior authorization of EVI and ICGEB*

[figure not shown][figure not shown]

signs for every 30 minutes till 3 hours post-vaccination from pre-vaccination will be calculated and tabulated for each vaccine group.

The investigator will check the biological parameters (haematology and serum chemistry). Newly occurring or worsening lab abnormalities will be assessed and reported by the investigator as adverse events as applicable. Clinical laboratory results will be tabulated by vaccine group at each time point as both quantitative parameters (raw values) and qualitative parameters (relative positions regarding normal ranges in use in the laboratory). Serious adverse events and discontinuation due to adverse event(s) will be described in detail by vaccine group.

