Information contained in this publication is the property of EVI and ICGEB and is confidential and will not be disclosed to third parties without written authorization from EVI and ICGEB. No part of this document may be reproduced, stored in a retrieval system or transmitted in any form or by any means -electronic, mechanical, recording or otherwise - without the prior authorization of EVI and ICGEB

[figure not shown][figure not shown]

**APPENDIX B-1: JAIVAC\_1\_1\_09 ACCEPTABLE LIMITS FOR 'OUT OF RANGE'  
LABORATORY PARAMETER(S) AT SCREENING/BASELINE**

| Sr #                   | Analyte             | Units   | Ref Lo                                                                                                    | Ref Hi |
|------------------------|---------------------|---------|-----------------------------------------------------------------------------------------------------------|--------|
| Haematology     |                     |         |                                                                                                           |        |
| 1                      | Haematocrit         | %       | If outside range as per Appendix B, then the value is to be co-related with other relevant lab parameters |        |
| 2                      | Haemoglobin         | gm / dl | 13.0                                                                                                      | 18.0   |
| 3                      | RBC Count           | 10E6/ul | 4.0                                                                                                       | 7.0    |
| 4                      | MCV                 | fL      | If outside range as per Appendix B, then the value is to be co-related with other relevant lab parameters |        |
| 5                      | MCH                 | pg      | If outside range as per Appendix B, then the value is to be co-related with other relevant lab parameters |        |
| 6                      | MCHC                | gm%     | If outside range as per Appendix B, then the value is to be co-related with other relevant lab parameters |        |
| 7                      | WBC count           | 10E3/ul | 4.0                                                                                                       | 11.0   |
| 8                      | % Neutrophils       | %       | 40.0                                                                                                      | 75.0   |

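### Comparing safety with the control vaccine is a primary objective, but section 11.5.1 rules out any between-group comparison, and the baseline-referenced laboratory endpoint has no change or shift summary

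*Supplement*

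**What the plan says.** **Comparison with control.** Section 3.1 lists as its second primary objective "To compare the safety of three (3) different dosages of JAIVAC-1 vaccine" with that of the Hepatitis B vaccine. Section 8.1 repeats that evaluating the safety of the three injections "in comparison with that of the control vaccine (Hepatitis B vaccine) is the primary objective of this study". Section 11.5.1, and the synopsis in the same terms, then states "The analysis shall be descriptive as the sample size does not allow any comparison between groups". Section 11.1.1 promises description across the vaccines but names no difference, ratio or interval. The 95% intervals in 11.5.1, 11.5.1.2 and 11.5.1.3 are all for proportions within one vaccine group.

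**Laboratory safety.** Section 4.6.1 defines one primary endpoint as "Biological safety, 28 days after each vaccination, in reference with the baseline before the first dose". The footnotes to Table 1 make the screening sample that baseline; for haematology it serves for eligibility "as well as baseline assessments for safety end-points since haematology assessments will not be done on Day 0 (pre-vaccination". For the analysis, section 11.5.1.3 says "Clinical laboratory results will be tabulated by vaccine group at each time point as both quantitative parameters (raw values") and by position against the normal range. The same section does plan change from pre-vaccination for vital signs, and 11.5.1.4 compares antibody levels with Day 0. New or worsening laboratory abnormalities are left to the investigator to report as adverse events where applicable.

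**Demographics.** Section 11.5.1.1 says "Group comparisons will be performed to confirm whether the vaccine groups are similar with regard to demographic characteristics".

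**The concern.** One third of the subjects (15 of 45) are randomised to a control vaccine so that dosages can be compared with it. The analysis section then declares the comparison impossible and gives sample size as the reason. That reason supports leaving out tests. It does not support leaving out an estimate. A reader of the report would have to form the contrast from separate group percentages, with no interval showing how little or how much the data exclude.

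The laboratory endpoint has a similar gap. It is worded as a within-subject reference to baseline, and the baseline is collected, but the listed tables describe each visit separately. Entry limits are wider than the reference range for many analytes, so an out-of-range value after vaccination need not be new.

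The demographic sentence adds an inconsistency. Groups are compared on baseline characteristics, which are not an endpoint, while comparison is excluded for safety, where an objective calls for it.

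**Working it through.** **1. The plan's own figure.** Section 11.1.1: 3 cohorts x (10 test + 5 control) = 45, that is 30 test and 15 control. This reproduces. No alpha, power, effect size or event rate is given, so there is no power statement to check.

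**2. What the within-group intervals show.** The exact upper 95% limit for zero events in n subjects is 1 - 0.025^(1/n):

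| n | Group | Upper limit |
|---|---|---|
| 5 | control, one cohort | 52% |
| 10 | one dosage | 31% |
| 15 | all controls | 22% |
| 30 | all dosages | 12% |

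**3. Can a difference be estimated at this size?** Yes. The documents give no event rates, so the counts below are assumed. The Newcombe 95% interval for p1 - p2 = d, with Wilson limits (l1, u1) and (l2, u2), is

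lower = d - sqrt[(p1 - l1)^2 + (u2 - p2)^2], upper = d + sqrt[(u1 - p1)^2 + (p2 - l2)^2].

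Example, 5/10 v 3/15: the Wilson limits are 0.237 to 0.763 and 0.070 to 0.452, and d = 0.30.
Lower = 0.30 - sqrt(0.263^2 + 0.252^2) = 0.30 - 0.364 = -0.064.
Upper = 0.30 + sqrt(0.263^2 + 0.130^2) = 0.30 + 0.293 = 0.593.

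| Dosage | Control | Difference (points) | 95% CI (points) |
|---|---|---|---|
| 5/10 | 3/15 pooled | +30 | -6 to +59 |
| 5/10 | 1/5 own cohort | +30 | -20 to +61 |
| 1/10 | 0/15 pooled | +10 | -12 to +40 |
| 1/10 | 0/5 own cohort | +10 | -34 to +40 |
| 0/10 | 0/15 pooled | 0 | -20 to +28 |

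The intervals are wide, but they can be reported. Pooling controls mainly tightens the lower limit. For context, power to detect an assumed 20% v 50% is 17% (5 controls v 10), 35% (15 v 10) and 49% (15 v 30). Having no test is therefore reasonable.

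**4. Entry limits against the reference range.** Appendix B has 24 haematology and chemistry analytes. Set against Appendix B-1:

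- Wider numeric limits (10): haemoglobin (lower 13.0 v 13.5), RBC, WBC, eosinophils, platelets (upper 500 v 400), total bilirubin (1.2 v 0.99), indirect bilirubin, direct bilirubin, creatinine, gamma-GT. For creatinine and gamma-GT the only change is that the lower limit falls to zero (from 0.7 and from 10).
- No numeric limit, to be judged with other parameters (7): haematocrit, MCV, MCH, MCHC, basophils, lymphocytes, monocytes.
- Not widened (7): neutrophils, sodium, potassium, glucose, AST, ALT, alkaline phosphatase.

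10 + 7 = 17 of 24. This counts what is permitted, not how many subjects will be out of range.

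**5. Do counts at baseline and at the visit settle it?** If b of n are out of range at screening and v at a later visit, the number newly out of range lies anywhere from max(0, v - b) to min(v, n - b). With assumed b = 2, v = 2 and n = 10, that is 0 to 2. The two counts do not identify the new cases; a shift table does.

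**6. Baseline comparison of demographics.** If a two-sample t-test were used (the protocol names none), power for a 1-SD difference at two-sided 5% would be 39% (10 v 5) or 65% (10 v 15). A non-significant result would not confirm similarity.

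**The case against.** A descriptive first-in-human study with no hypothesis test is acceptable, and the 11.5.1 sentence stands under a heading about hypothesis testing, so it can be read as excluding inference only. Group proportions with intervals set side by side are a form of comparison. A reader might infer that the trial would leave objective 2 wholly unanswered. The documents do not support that, because a descriptive answer would be available. What remains is that the sentence excludes every comparison, the objective asks for one, and no effect measure is named. Because 11.5.1 excludes comparison outright, this cannot be put down to detail left for the SAP. Wide intervals do show limited information, and showing that is part of the answer.

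On laboratory data the objection carries more weight. Section 11 calls itself an outline and promises a separate SAP, which is not among the documents, and change and shift tables could appear there. Screening results would be tabulated next to later visits. Exclusion criterion 11 removes other clinically significant abnormal values, and new or worsening abnormalities can become adverse events. So it would be wrong to infer that the laboratory tables would attribute pre-existing abnormalities to vaccination, or that the plan holds nothing but raw within-group summaries. However, the adverse-event route depends on the judgement of an investigator who knows the allocation (section 4.5), and paired counts cannot replace a shift table (step 5).

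Pooling controls is also open to challenge. Randomisation is cohort-specific (section 4.4), and each cohort starts at least 21 days after the last first dose of the one before (section 4.1). In favour of pooling, every control receives the same product, volume and schedule from a single batch (section 6.1.2).

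**Conclusion.** The point holds in two parts of unequal strength.

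- **Firm:** sections 3.1 and 8.1 make comparison with control a primary objective, and 11.5.1 excludes it. No between-group estimate is planned beyond side-by-side proportions with within-group intervals. The sample size justifies having no test, not the absence of an estimate.
- **Softer:** the laboratory endpoint is referenced to baseline, but the stated tables are not. With entry values allowed outside the reference range for up to 17 of 24 analytes, out-of-range counts alone could mix pre-existing and new abnormalities. How often this would happen among 45 healthy men cannot be told from the documents, and the SAP might close the gap.

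The demographic sentence is a minor inconsistency. The interval widths rest on assumed event counts; the analyte count and the conflict between sections do not. The change should be made, but the design itself is not at fault.

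**What to change.** 1. In 11.5.1 and the synopsis, replace the sentence excluding comparison with one saying that no hypothesis tests will be performed.
2. In 11.5.1.2 and 11.5.1.3, for each solicited reaction, any grade 3 event and any new laboratory abnormality, report the difference in proportions for each dosage minus the 15 pooled controls, with a 95% score or exact interval labelled as estimation only. Show own-cohort controls alongside as a check, because randomisation is cohort-specific.
3. In 11.5.1.3, add change from the screening baseline for each analyte and visit, and low/normal/high shift tables by dosage and visit with controls shown.
4. In 11.5.1.1, describe demographics by group and delete the comparison meant to establish similarity.

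The cost is wording and a few more tables from data already collected, with no added subjects, samples or visits. The intervals will be visibly wide, and the pooled controls will have been enrolled at different times. Rewording objective 2 as descriptive would also remove the contradiction, but would give up the estimate that the control arm can supply.
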